#### 2.9.3. Reported Adverse Events

Following each immersive virtual reality session, participants will be assessed for the presence of signs and symptoms associated with technology use (cybersickness), such as dizziness, nausea, headache, disorientation, or general discomfort. The systematic recording of these events will ensure participant safety, provide feedback to the research team, and help prevent situations that could compromise participant well-being. All adverse events will be classified according to type, severity, and their relationship to the intervention, and will be documented in a dedicated registry for subsequent analysis.

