#### 2.6.3. Safety During the Intervention

The implementation of the immersive virtual reality (IVR) intervention will be conducted under strict clinical safety measures aimed at safeguarding the physical integrity and well-being of participants. Prior to the formal initiation of the program, a familiarization session will be conducted to provide standardized instructions regarding device use, characteristics of the virtual environment, and potential symptoms associated with the immersive experience, such as dizziness, nausea, or fatigue.

During each session, the professional team will ensure continuous supervision of participant performance and tolerance, monitoring for signs of postural instability, physical discomfort, or disorientation. In the event of any adverse event, the fall and emergency response protocol will be immediately activated, establishing clear procedures for first aid, notification, and referral to emergency services when required.

Additionally, symptoms associated with virtual reality use (cybersickness) will be systematically assessed using validated instruments, allowing for the documentation of their frequency, intensity, and relationship to the intervention. This structured monitoring strategy contributes to ensuring participant safety and to rigorously documenting adverse events as part of the study’s feasibility indicators.

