#### 2.7.3. Monitoring of Adverse Events

To ensure the relevance, safety, and acceptability of the virtual reality (VR) program and the targeted interventions among older adults, the following technical and user-centered criteria are established:Environmental Preparation:

An appropriate physical space is essential to promote concentration and minimize risks. In this regard, it is necessary to: Ensure an obstacle-free environment that does not compromise physical safety during the experience. Guarantee adequate lighting, comfortable temperature, and proper ventilation to facilitate participation of older adults, and minimize environmental noise to enhance immersion during the session.

2.Device Placement and Adjustment:

The responsible professional must: Demonstrate how to wear the headset and use the controllers. Adjust the device individually to ensure comfort, stability, and proper visualization of the virtual environment. Verify that the user maintains a safe posture throughout the experience. For participants who wear prescription glasses, an appropriate spacer accessory will be incorporated to extend the headset.

3.User Preparation:

Before initiating the session, participants must be provided with clear and comprehensible information, delivered in verbal, visual, and auditory formats. Specifically, the following is recommended: Participants will undergo monitoring of physiological parameters, particularly blood pressure, at the beginning and at the end of the session. Additionally, the functioning of the virtual reality (VR) device and the characteristics of the experience must be explained precisely. Participants should be informed about possible sensations that may be experienced (e.g., immersion, mild dizziness, or initial disorientation). Any questions should be addressed and concerns managed throughout the virtual experience.

4.Monitoring During the Session:

Continuous supervision is essential to prevent adverse events. Accordingly, it is necessary to: Continuously observe the user’s physical and emotional responses. Identify signs of discomfort, anxiety, fatigue, or distress (e.g., nausea or postural instability) associated with cybersickness. Immediately interrupt the session if the participant requests it or if any adverse reaction is detected.

5.Post-Session Evaluation:

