At the conclusion of the intervention session, a comprehensive evaluation should be conducted, including the collection of the user’s subjective perception of the experience. Preliminary assessment of the impact of VR on variables related to fall prevention (e.g., balance, confidence in gait, or reaction time). Administration of the Simulator Sickness Questionnaire (SSQ) and systematic documentation of clinical observations by the multidisciplinary professional team.

6.Action Protocol for Falls and Emergencies

This protocol establishes the procedures designed to ensure a timely, effective, and efficient response to adverse events occurring during the implementation of project activities. Its primary purpose is to safeguard the physical integrity and well-being of participants by ensuring high-quality care through the appropriate use of available human and material resources.

The adverse and/or sentinel events considered within this protocol include, but are not limited to, falls, loss of consciousness, wounds, traumatic injuries, and any other situation that may compromise the participant’s physical stability.

The professional team will be responsible for activating and implementing the action protocol in the event of a critical or adverse incident, as well as for carrying out the corresponding notification in accordance with institutional guidelines.

In the event of an incident, the following procedures must be followed:(a)A member of the multidisciplinary healthcare team shall provide first aid to the affected participant, assessing their general condition and ensuring basic stabilization measures.(b)Simultaneously, another team member shall contact the appropriate emergency service, clearly and accurately reporting the nature of the incident, the participant’s condition, and the exact location.(c)The professional in charge shall communicate with the participant’s registered emergency contact, informing them of the incident, the actions taken, and any potential referral to a healthcare facility.(d)Subsequently, the incident must be formally reported to the project coordination team, with written documentation completed in accordance with established administrative procedures.

These criteria are aligned with the protocols used by healthcare services, specifically within Family Health Centers (CESFAM), primary care facilities in which older adults actively participate as a priority user population.

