In accordance with the previously developed theoretical and empirical foundations, the virtual reality sessions designed for the fall prevention program in older adults would be structured according to the criteria presented in Table 2.

Following the immersive virtual reality intervention sessions, each participant will be assessed for adverse symptoms related to technology use (cybersickness), to ensure user safety, provide feedback to the research team, and prevent potential situations that could compromise participant well-being [35].

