**Figure 7 ijerph-23-00504-f007:**
[figure not shown]
A quasi-experimental Virtual Reality-Based Program for Fall Risk Reduction in Older Adults in Primary Health Care.

**Table 1 ijerph-23-00504-t001:** Inclusion and exclusion criteria.

Inclusion Criteria	Exclusion Criteria
○ Age ≥ 60 years.	○ Progressive neurological diseases or major neurocognitive disorders.
○ Functional status classified according to EFAM and the Barthel Index: autonomous older adults without risk or with mild risk of dependency.	○ Uncompensated sensory impairments.
○ Mild frailty according to Fried’s criteria or low handgrip strength (men < 27 kg; women < 16 kg).	○ Recent history of severe fractures or traumatic brain injury (TBI).
○ Timed Up and Go (TUG) test between 10 and 20 s. ○ Falls Efficacy Scale–International (FES-I) score between 20 and 40 points.	○ IMC ≥ 35.
○ Activities-specific Balance Confidence (ABC) Scale score ≥ 67%. ○ Dizziness Handicap Inventory (DHI) score ≥ 30 points. ○ Older adults who have not received interventions aimed at fall prevention or cognitive function stimulation for at least six weeks prior to study enrollment.	○ Decompensated heart disease or uncontrolled cardiac arrhythmias.
○ Provision of written informed consent.	
○ Adequate tolerance to visual and auditory stimuli.	

**Table 2 ijerph-23-00504-t002:** This is a table of Virtual Reality-Based Program for Fall Risk Reduction in Older Adults in Primary Health Care.

Activities/Exercises	Time	Description
Equipment set-up and safety check	−Pre-start to +3 min from session onset	Brief instructions, device adjustment, verification of safe area, and confirmation of participant readiness.
Warm up	5 min.	Use of exercises based on the Fall Prevention Manual for Older Adults and the Wheel within the VIVIFRAIL Program (Categories B, C1, C2, and D)
Balance 1	5 min.	Balance exercises; trunk control exercises, Weight shifting and functional reaching.
Balance 2	8 min.	Balance exercises, trunk control exercises, dynamic balance, locomotion, spatial coordination.
REST/transition	3 min.	Rest.
Balance 3	8 min.	Balance exercises, trunk control exercises, dynamic balance, locomotion, spatial coordination.
Balance 4	5 min.	Balance exercises, trunk control exercises, dynamic balance, locomotion, spatial coordination. Functional mobility.
REST/transition	3 min.	Rest.
Vestibular	8 min.	Vestibular exercises, depending on the needs of the participating older adults.
ADL	5 min.	Daily life-based exercises.

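### Cybersickness is scored only after VR sessions in participants selected for dizziness handicap, so the planned judgement of relationship to VR has no session-level reference

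*Protocol article*

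**What the plan says.** The Abstract names cybersickness as a feasibility indicator, next to recruitment, adherence and retention. Wherever the timing of its measurement is given, it falls after exposure:

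- Section 2.9.3: "Following each immersive virtual reality session, participants will be assessed for the presence of signs and symptoms associated with technology use (cybersickness".
- Section 2.7.5: "Following the immersive virtual reality intervention sessions, each participant will be assessed for adverse symptoms related to technology use (cybersickness".
- Section 2.7.3, under the post-session item: "Administration of the Simulator Sickness Questionnaire (SSQ) and systematic documentation of clinical observations by the multidisciplinary professional team".

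Two other measurements sit near it in section 2.7.3. Physiological parameters are taken twice: "Participants will undergo monitoring of physiological parameters, particularly blood pressure, at the beginning and at the end of the session". During the session, staff are to watch the participant: "Identify signs of discomfort, anxiety, fatigue, or distress (e.g., nausea or postural instability) associated with cybersickness".

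Section 2.6.3 says that structured cybersickness assessment serves its purpose by "allowing for the documentation of their frequency, intensity, and relationship to the intervention". Section 2.9.3 adds that adverse events will be classified by type, severity and relationship to the intervention.

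On the population, Table 1 lists "Dizziness Handicap Inventory (DHI) score ≥ 30 points" among the inclusion criteria. Section 2.7.2 measures the DHI in the pre-intervention assessment, as the instrument for vestibular symptoms. Section 2.7.6 describes the conventional workshops and mentions no symptom questionnaire.

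**The concern.** Entry selects people on a dizziness scale, and the indicator then counts dizziness, nausea and disorientation. A score taken once, after the session, mixes symptoms the participant brought along with symptoms the session produced. To judge relationship to VR, the assessor needs to know the participant's state just before the session, or what comparable people report after the same exercise without a headset. The article describes neither.

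The exercise content adds to the difficulty. The VR programme includes head rotations, body turns and a vestibular block (section 2.7.5, Table 2). These could provoke symptoms without a headset.

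At stake is whether the trial can say how well VR is tolerated in primary care, which is part of its stated purpose. The omission is one of data collection: no later analysis can recover a pre-session score that was not taken.

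**Working it through.** The plan gives no rate, threshold or calculation for cybersickness, so there is no figure of its own to reproduce. The check has two parts.

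**1. What reference each planned record gives for one session**

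| Record | Where | Before the session? | Symptom score? |
|---|---|---|---|
| SSQ | 2.7.3, post-session item | Not described | Yes |
| Blood pressure and similar | 2.7.3, user preparation | Yes, and at the end | No |
| Staff observation | 2.7.3, during the session | No | No |
| DHI | 2.7.2 | Once, before the programme | Yes, but a different instrument and not per session |
| Symptoms in the conventional arm | 2.7.6 | Not described | Not described |

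No row supplies a symptom score for the same person just before the same session, or a parallel score without VR.

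**2. Illustration of what this can do to the rate**

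Inputs from the article: 20 participants in the VR arm (section 2.3); 12 weeks at two sessions per week (section 2.7.4), so 24 sessions each and 20 × 24 = 480 planned VR sessions.

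Inputs assumed, because the article gives none: p0, the probability that a symptom is present before a session; and pv, the probability that VR produces a symptom in someone who had none. I also assume that the two act independently and that a session does not relieve existing symptoms.

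- Post-session positive rate = 1 − (1 − p0)(1 − pv)
- Share of positives already symptomatic = p0 / post-session rate

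| p0 | pv | Post-session rate | Positive of 480 | Share already symptomatic |
|---|---|---|---|---|
| 0.10 | 0.10 | 1 − 0.90 × 0.90 = 0.19 | 91 | 0.10/0.19 = 53% |
| 0.30 | 0.10 | 1 − 0.70 × 0.90 = 0.37 | 178 | 0.30/0.37 = 81% |
| 0.50 | 0.10 | 1 − 0.50 × 0.90 = 0.55 | 264 | 0.50/0.55 = 91% |
| 0.30 | 0 | 1 − 0.70 × 1.00 = 0.30 | 144 | 100% |

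The second and fourth rows make the point: 37% with a VR effect and 30% with none are both plausible results, and a post-session score alone cannot say which situation produced them. With a pre-session score, the second row resolves. About 480 × 0.70 = 336 sessions start symptom-free, about 480 × (0.37 − 0.30) = 34 of them become positive, and 34/336 returns the assumed 10%.

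**The case against.** A reader might infer that the plan simply counts existing dizziness as caused by VR. The article does not say that. Sections 2.6.3 and 2.9.3 both provide for relationship to the intervention to be documented, so a causality step is planned. What is missing is session-level information to base it on.

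A reader might also infer that the post-session SSQ is uninformative. It is not: it documents how often and how strongly symptoms occur after sessions. Only their attribution is weakened.

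There are partial safeguards. Baseline DHI gives a person-level reference. Table 2 opens each session with a readiness check, staff observe throughout, Session 0 is monitored for symptoms, and Table 1 requires tolerance of visual and auditory stimuli. These help the judgement, but none shows whether a given symptom preceded a given session.

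On the control arm, the plan defines cybersickness through use of technology and treats it as a descriptive indicator with no between-arm comparison. A control checklist is therefore useful but not essential. Nor is the arm without safety recording: the fall and emergency procedure in section 2.7.3 covers all project activities.

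Finally, this is a condensed article, and a pre-session SSQ is not expressly excluded. That has some force. However, section 2.7.3 specifies before-and-after measurement for blood pressure and places the SSQ only at the end, and three sections agree on post-session timing. The schedule as stated is post-session.

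**Conclusion.** The concern holds in a limited form. The SSQ is scheduled only after VR sessions, in people required to have DHI ≥ 30, with no pre-session score and no control-arm symptom record described. The planned relationship classification therefore lacks a session-level reference. Existing dizziness may be misattributed to VR, and the cybersickness rate may be overstated.

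That it will be overstated is not established. A judgement made without a reference can also err the other way, if staff put a true reaction down to the participant's usual dizziness.

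The size is unknown. The 53–91% range rests wholly on assumed rates, and a single handicap score is not a daily symptom rate. That every participant enters with dizziness handicap also assumes that a higher DHI means more handicap; the article does not give the scoring direction. Whether the DHI line in Table 1 is as intended is a separate question.

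The consequence is confined to one descriptive feasibility indicator. The primary TUG analysis is not affected.

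**What to change.** Give the same SSQ immediately before as well as after VR sessions, at least at Session 0 and the early sessions. Report the post-minus-pre change, or the proportion with new or worsened symptoms, as the cybersickness indicator, and keep the raw post-session scores beside it. State that the relationship classification will use the pre-session score and baseline DHI.

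Optionally, use the same brief symptom checklist in the conventional sessions, as a reference for symptoms due to exercise.

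The cost is a few minutes per session for an instrument already in use. Time is tight: the items in Table 2 add up to 3 + 5 + 5 + 8 + 3 + 8 + 5 + 3 + 8 + 5 + 5 = 58 of the 60 minutes, so the pre-session form fits best before the clock starts. Doing it at every session means 480 extra forms. Limiting it to Session 0 and, say, the first four sessions means 20 × 5 = 100.

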#### 2.9.4. Intervention Adherence

Intervention adherence is defined as the percentage of intervention sessions effectively completed by each participant relative to the total number of sessions planned in the protocol. This indicator will be used to assess the level of compliance and active participation of participants in the intervention. Based on the study design, a minimum adherence rate of 80% is expected in both the experimental and control groups (*n* = 32).

## 3. Expected Results

Pre- and post-intervention assessments will be conducted across functional, physical, and emotional domains. These assessments will be administered by trained health care professionals who will not be involved in the delivery of the interventions, thereby ensuring the independence of the evaluation process. In both the experimental and control groups, a system of rotating evaluators will be implemented to enhance objectivity and minimize potential assessment bias.

In addition, an assessment blinding process will be implemented. Scoring batches will be randomized, and standardized training and inter-rater reliability protocols will be established. Evaluators will work with alphanumeric identifiers (IDs) and a coded temporal marker, so that pre- and post-intervention conditions will not be identifiable during the data analysis process.

The primary outcome of this study is a reduction in fall risk among older adults at risk of frailty, as measured by the Timed Up and Go (TUG) test. This change is expected to be more pronounced in the experimental group compared with the control group.

As secondary outcomes, the experimental group is expected to demonstrate a significant reduction in concern about falling, as measured by the Falls Efficacy Scale–International (FES-I), and an increase in balance-related confidence, assessed using the Activities-specific Balance Confidence (ABC) Scale. Improvements in physical performance are also anticipated, including static balance, gait speed, and lower-limb strength, as evaluated through the components of the Short Physical Performance Battery (SPPB), including the chair stand test. In addition, maintenance of handgrip strength, assessed through handgrip dynamometry, is expected. Taken together, these outcomes are anticipated to be more pronounced in the experimental group, reflecting the potential effects of the proposed intervention.

### 3.2. Secondary Outcomes

#### Concern About Falling

*Falls Efficacy Scale–International (FES-I):*

The Falls Efficacy Scale–International (FES-I) was developed to provide a comprehensive measure of concern about falling, incorporating both physical and social factors, while ensuring suitability for cross-cultural applications. Available evidence strongly supports its use in older adult populations [43]. The FES-I consists of 16 items in which participants rate their level of concern about the possibility of falling in different situations, using a scale ranging from 1 (not at all concerned) to 4 (very concerned). A total score greater than 23 is commonly considered indicative of elevated or clinically relevant concern regarding fall risk [44].

In the present study, is expected on experimental group to show a 3-to-6-point reduction in total FES-I scores, with a lower proportion of participants scoring > 23, reflecting a small-to-moderate effect size (d ≈ 0.40–0.60). This improvement would indicate enhanced perceived self-efficacy and reduced activity restriction due to fear of falling [44].

*Activities-specific Balance Confidence (ABC) Scale:*

The ABC questionnaire consists of 16 items and may be self-administered or applied by a trained evaluator. It is a widely used subjective measure designed to assess balance confidence and the degree of fear of falling experienced by an individual when performing various daily activities, such as moving around the home, ascending or descending stairs, getting into or out of a car, or bending down to pick up objects from the floor, among others [45]. Participants rate their confidence in performing each activity without losing balance or becoming unsteady, generating a total score expressed as percentage, with higher values indicating greater balance confidence.

In this study, changes in total ABC score will be analyzed to evaluate the effect of the intervention on balance-related confidence. A value ≥ 67% has been associated with lower fall risk in community-dwelling older adults and will be considered clinically relevant threshold. Improvements in total score, as well as an increase in the proportion of participants reaching value ≥ 67%, will be interpreted as reflecting enhanced perceived safety and functional confidence during activities of daily living. A small-to-moderate effect size (d ≈ 0.40–0.70) is anticipated,

*Short Physical Performance Battery (SPPB):*

The Short Physical Performance Battery (SPPB) includes three sequential performance-based tests administered over approximately 6–12 min: static balance (feet together, semi-tandem, and tandem), gait speed over 2 or 4 m, and the five-repetition chair stand tests [46].

The experimental group is expected to achieve a clinically meaningful increase of ≥1 point in the total SPPB score, with a small-to-moderate effect size (d ≈ 0.40–0.70), reflecting improved lower-extremity function and overall functional stability.

*Handgrip Dynamometry:*

Muscle strength can be assessed using various procedures; however, handgrip strength measurement has become one of the most used tools in epidemiological studies due to its ease of administration, high reliability, and low cost. These characteristics make it a relevant health biomarker, with wide applicability in both clinical settings and population-based research [47]. In Chile, a study conducted by Lera et al. evaluated 5255 adults aged 60 years and older, reporting muscle weakness cut-off points of ≤27 kg for men and ≤15 kg for women [48].

In the present study, handgrip strength will be measured at baseline and post-intervention to examine potential changes associated with the immersive virtual reality program. Stability or attenuation of decline in handgrip strength in the experimental group, compared with the control group, will be interpreted as reflecting preservation of overall muscular function within the context of fall risk prevention.

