**H3:** 
*Older adults receiving the intervention will demonstrate a significant increase in balance-related confidence, as assessed by the Activities-specific Balance Confidence (ABC) Scale, compared with the control group.*

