### 2.4. Participant Recruitment

Participant recruitment will be conducted across the different groups affiliated with primary health care (PHC) services in the municipality of San Pedro de la Paz, Biobío Region, Chile.

The recruitment process will be carried out by trained research support staff. Initial contact will be made by telephone with the representatives of the participating groups, followed by the coordination of in-person visits to the locations where group activities take place. During these visits, older adults will be invited to participate in the study and will be provided with clear and comprehensible information regarding the study objectives, the general characteristics of the virtual reality (VR) intervention, its duration, and the associated assessment procedures. Emphasis will be placed on the voluntary nature of participation and on the participants’ right to withdraw from the study at any time without consequences.

Older adults who express interest in participating will be assessed to verify compliance with the established eligibility criteria. Final inclusion in the study will occur only after the informed consent form has been signed, ensuring adherence to the ethical principles of autonomy, confidentiality, and safety for older participants.

To safeguard confidentiality and anonymity, participant identification data will be coded using alphanumeric identifiers. These codes will also be used to differentiate between pre- and post-intervention measurements.

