#### 2.7.2. Pre-Intervention Assessment (Phase 1)

As part of the program implementation, a pre-intervention assessment will be conducted, focusing on the evaluation of multiple functional and perceptual components. Vestibular-related symptoms will be assessed using the Dizziness Handicap Inventory (DHI). Physical performance will be evaluated through handgrip dynamometry, while functional mobility will be assessed using the Timed Up and Go (TUG) test and the Short Physical Performance Battery (SPPB). Functional status will be measured using the Barthel Index and the Instrumental Activities of Daily Living scale by Hernández and Neumann. The psychological dimension associated with falls will be evaluated using the Falls Efficacy Scale–International (FES-I) and the Activities-specific Balance Confidence (ABC) Scale.

A maximum period of two weeks will be established for the completion of all baseline assessments. Following this period, minimum eligibility criteria for participation in the intervention will be confirmed prior to the initiation of the immersive virtual reality-based intervention.

Regardless of group allocation (control or experimental), each intervention session will follow the structured schedule described in Table 2, with a total duration of 60 min (including preparation, warm-up and cool-down phases, exercises, and rest periods). According to the Manual for Fall Prevention in Older Adults [32], sessions should focus on exercises targeting muscle strengthening, static and dynamic balance, weight-shifting activities, stretching exercises, functional reaching tasks, strength training, and postural control responses, including righting, support, and balance reactions. In addition, the intervention will be adapted according to participants’ interests, preferences, difficulty level, and individual functional profiles.

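### ABC ≥ 67% is both an entry requirement and the threshold whose attainment is to be read as improvement, so the planned increase in that proportion cannot occur

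*Protocol article*

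**What the plan says.** Table 1 lists, as an inclusion criterion with no alternative attached, "Activities-specific Balance Confidence (ABC) Scale score ≥ 67" (in percent).

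Section 3.2, under the ABC scale, gives the same value as the yardstick for the outcome: "A value ≥ 67% has been associated with lower fall risk in community-dwelling older adults and will be considered clinically relevant threshold". It then says that "an increase in the proportion of participants reaching value ≥ 67%, will be interpreted as reflecting enhanced perceived safety and functional confidence". The same paragraph also plans the continuous analysis: "changes in total ABC score will be analyzed to evaluate the effect of the intervention on balance-related confidence".

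H3 in the Introduction predicts that the intervention group "will demonstrate a significant increase in balance-related confidence", compared with control.

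On timing, section 2.4 says "Older adults who express interest in participating will be assessed to verify compliance with the established eligibility criteria". Section 2.7.2 places the "Falls Efficacy Scale–International (FES-I) and the Activities-specific Balance Confidence (ABC) Scale" in the pre-intervention assessment and continues: "Following this period, minimum eligibility criteria for participation in the intervention will be confirmed prior to the initiation".

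Section 2.8 tests group × time by repeated-measures ANOVA and includes the ABC among four Holm-adjusted secondary outcomes, which it describes as supportive and exploratory.

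**The concern.** An outcome threshold is informative only if some participants can cross it. Here everyone must already be on the favourable side to enter. The change that section 3.2 names as a sign of benefit is excluded by the eligibility rule, and the only movement left is downward. A report that follows section 3.2 literally would have to present an unchanged or falling proportion against a stated expectation of a rise, whatever the programme does.

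A second, smaller consequence concerns the continuous score. Entry at 67 or above removes the lower two thirds of the scale at baseline, and people near 100 have little or nothing to gain. This limits how much improvement H3 can show.

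**Working it through.** **1. The proportion at baseline**

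Inputs: entry requires ABC ≥ 67% (Table 1); the outcome threshold is ≥ 67% (section 3.2); there are 20 participants per group (section 2.3); the ABC is measured at baseline and eligibility is confirmed afterwards (section 2.7.2).

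- Baseline proportion at or above 67%, given entry at or above 67%: 20/20 = 100% per group, 40/40 overall.
- Largest possible increase: 100% − 100% = 0 percentage points.

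This step needs no distributional assumption.

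**2. Is the overlap peculiar to the ABC?**

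| Measure | Entry range (Table 1) | Outcome cut-off (sections 3.1, 3.2) | Crossing in the favourable direction possible? |
|---|---|---|---|
| TUG | 10–20 s | > 13.5 s signals raised risk | Yes |
| FES-I | 20–40 points | > 23 signals elevated concern | Yes |
| ABC | ≥ 67% | ≥ 67% signals lower risk | No |

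Only the ABC has this conflict.

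**3. What the proportion would do after 12 weeks (illustration)**

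The article gives no mean or SD for the ABC, so these are assumptions: normal scores in the source population, three mean/SD pairs, and a pre–post correlation ρ of 0.5 (the value section 2.3 uses for the sample size) or 0.8. The post score is simulated as mean + ρ × (pre − mean) + √(1 − ρ²) × SD × noise + d × SD, among people with a pre score of 67–100. Section 3.2 anticipates d of about 0.40–0.70; d is taken here in source-population SDs.

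| Mean, SD | ρ | d = 0 | d = 0.4 | d = 0.7 |
|---|---|---|---|---|
| 70, 15 | 0.5 | 71.0% | 83.9% | 90.7% |
| 70, 15 | 0.8 | 81.9% | 93.0% | 97.3% |
| 75, 18 | 0.5 | 75.5% | 87.2% | 92.9% |
| 75, 18 | 0.8 | 84.3% | 94.3% | 97.9% |
| 80, 12 | 0.5 | 89.3% | 95.3% | 97.7% |
| 80, 12 | 0.8 | 93.1% | 97.9% | 99.3% |

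The pre-intervention figure is 100% in every row. The proportion falls in every cell, including those with the anticipated gain.

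**4. What a real benefit would look like**

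In the first row, take d = 0 for control and d = 0.4 for intervention. The falls are 100 − 71.0 = 29.0 and 100 − 83.9 = 16.1 points. The difference of 83.9 − 71.0 = 12.9 points favours the intervention, but it appears as a smaller loss and not as the increase that section 3.2 describes.

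**5. Sample size**

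The article's minimum of 34 reproduces with a noncentral F for the group × time interaction: λ = f² × N × m / (1 − ρ) = 0.0625 × 34 × 2 / 0.5 = 8.5, with df 1 and 32, gives power 0.807; N = 32 gives 0.781. Inflating for 15% attrition, 34/0.85 = 40. None of this uses the ABC threshold.

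**The case against.** The strongest reply is that nothing formal depends on the proportion. H3 is a comparison with control, section 3.2 plans the analysis of total-score change, and section 2.8 supplies the group × time test. No test of the proportion is planned. The clause is one line of interpretation for a supportive outcome. All of this stands, and it limits the point to that clause and to the reduced headroom.

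Three stronger readings are tempting, but the article does not support them.

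- *H3 cannot be tested, or an effective programme would look harmful.* That follows only from an uncontrolled pre–post reading of the proportion. Both arms share the entry cut-off, so regression to the mean is expected in both and largely cancels in the planned comparison. The cancellation is not guaranteed, because allocation is by pre-existing groups (section 2.2).
- *ABC scores can vary only over 67–100, so the anticipated d can be converted to points.* The confinement holds at baseline only; later scores can fall below 67. The article gives no ABC standard deviation and does not say which one standardises d.
- *The inequality in Table 1 is the wrong way round.* Section 3.2 does link values at or above 67% with lower fall risk, while the programme aims to reduce fall risk, so checking the line is reasonable. Nothing in the article establishes that it is an error.

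One escape remains: if the eligibility check in section 2.4 used an ABC measurement separate from the baseline one, the baseline proportion could fall below 100%. The article describes no such second measurement, and section 2.7.2 confirms eligibility after the baseline assessments.

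**Conclusion.** The contradiction holds as written. The proportion at or above 67% is 100% in both arms at baseline, so an increase is impossible (maximum 0 percentage points). This rests on Table 1 being applied as printed and on the baseline ABC being the one that counts for eligibility. That some fall should be expected is a qualitative conclusion; the 71–99% range depends on the assumed means, SDs and correlations and is illustrative only.

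The total-score test of H3 is valid, with less room for improvement because baseline scores lie in 67–100. The TUG analysis and the sample size are untouched. This should be fixed, but because it concerns the interpretation of a supportive secondary outcome, it does not threaten the trial's main conclusion.

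**What to change.** Reconcile Table 1 and section 3.2 before anyone is screened.

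- If the Table 1 line stands: delete from section 3.2 the reading of an increased proportion at or above 67%, interpret the ABC only through the between-arm difference in total-score change (already the planned test), and state the restricted entry range as a limitation.
- If the Table 1 line is not what was intended: the sponsor must correct it, then check that the threshold reading in section 3.2 works with the corrected criterion. Which entry criterion is right is for the sponsor to decide.

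The cost is a sentence or two in section 3.2, or one line in Table 1, with no additional participants or assessments. Timing matters mainly for the second case, because an eligibility line cannot be repaired for people already enrolled.
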